### Evaluation and interventions

Volunteers are selected based on information from their medical records. They are first contacted through a telephone call to *ascertain* whether they fit the *inclusion criteria* and *do not meet any* of the *exclusion criteria*. They are then pre-selected and invited to participate in the study. Those who agree to participate are scheduled their first visit (visit 1) at the study site.

Eligible individuals go through a four-visit protocol as described below. Figure 1 shows the detailed flowchart of the study; Fig. 2 summarizes the recruitment, study interventions, and assessments; and Fig. 3 describes the study intervention (exercise and condition).

**Fig. 1 Fig1:**
[figure not shown]
Study design. IPAq: International Physical Activity Questionnaire; AE: aerobic exercise session; RE: resistance exercise session; CE: combined exercise; FMD: flow-mediated dilation; BFV: blood flow velocity; DBA: diameter of brachial artery; VR: vascular resistance

**Fig. 2 Fig2:**
[figure not shown]
Schedule of enrolment, interventions, and assessment. Adapted from SPIRIT Figure 2013. **Subjects will be allocated to perform twice (X-X) each exercise session on alpha-1 adrenergic block and placebo conditions. IPAq: International Physical Activity Questionnaire; BP: blood pressure; 1-RM: one-repetition maximum; BFV: blood flow velocity; DBA: diameter of brachial artery; FMD: flow-mediated dilation; ANS: autonomic nervous system. Study period: -t1, on-site screening (at Instituto de Cardiologia do Rio Grande do Sul/Fundação Universitária de Cardiologia – ICFUC), media postings, and patient databases; -t2, first visit of the volunteer to the research (ICFUC); -t3, second visit of the volunteer to the research (ICFUC); 0, contact with the independent researcher not involved with the study for volunteer randomization access; t1: pre-exercise assessments (10 min); t2, t3, t4: post-exercise session evaluation (10, 40, 70 min)

**Fig. 3 Fig3:**
[figure not shown]
Schedule of intervention day. BP: blood pressure; HR: heart rate; SBP: systolic BP; DBP: diastolic BP; ANS: autonomic nervous system; FMD: flow-mediated dilation; 1-RM: one-repetition maximum

Since the study is designed to assess the acute effects of different types of exercise types under the condition of α1-adrenergic blockade or placebo, female volunteers are to undergo evaluations and exercise sessions during the luteal phase of the menstrual cycle. One strategy to improve adherence to the study protocol is to provide the volunteers the results of their laboratory tests and clinical assessments (IPAq, blood pressure and anthropometric measurements, cardiopulmonary test, biochemical analysis, arterial stiffness, and endothelial function assessments and evaluation of ANS) when they complete the study protocol (after their last visit). In case of subject withdrawal, the results will be made available to the volunteers on demand upon study completion.

### Visit 1: interview, anthropometric assessment, and exercise test

Visit 1 takes place at the Laboratory of Clinical Investigation (LCI) at the study site. All inclusion and exclusion criteria are ascertained and the principal investigator ([name]) will provide the volunteers detailed information on the study and allow time for questions before asking them to sign a free and informed consent form. They will be asked whether they agree to the use of their data should they choose to withdraw from the trial. They will be also asked whether they give permission for the research team to share relevant data with staff from other universities taking part in the research or regulatory authorities, where applicable. This trial does not involve collecting biological specimens for storage. All research data collected will be stored in an appropriate safe space at the study site that is accessible to the principal investigator ([name]) only.

They are then administered a medical questionnaire the International Physical Activity Questionnaire – long version (IPAQ, http://www.ipaq.ki.se). The volunteer is asked to remain in a seated position in a quiet room for 5 min before their blood pressure (BP) is measured (OMRON™ HEM-714INT device, Tokyo, Japan); three recordings are taken 1 min apart on the arm with the highest values. Those who meet all inclusion criteria undergo an anthropometry assessment and a pre-scheduled exercise stress test.

The anthropometry assessment takes place at the study site. It includes measurements of total body mass (measured with appropriate one-piece [males] and two-piece clothing [females] in a standing position barefoot with feet together at the center of the scale); height (measured in a standing position with feet together, the head in the Frankfort plane with the stadiometer on the top of the head and readings taken while breathing in); waist circumference (measured in a relaxed standing position with arms folded across the chest with the measuring tape placed around the abdomen at the narrowest point between the lower costal margin and the upper part of the iliac crest, the reading is made in the front perpendicular to the longitudinal axis of the body) [29].

The exercise stress test is performed on a treadmill (Inbramed, Porto Alegre, Brazil) using the Bruce Protocol and following the Brazilian Society of Cardiology guidelines [30]. In a testing room at the study site, a qualified technician and a cardiologist conduct the stress test followed with measurements of maximum oxygen consumption, respiratory parameters, and maximum heart rate (HR) (ErgoPC 13, MICRIMED, Brasília, Brazil). Aerobic exercise is to be prescribed according to these measurements. The volunteers are then released by the cardiologist. They are contacted by phone to schedule visit 2.

### Visit 2: blood collection, assessment of arterial stiffness, and maximum strength test

On visit 2 the volunteers are asked to come to the study site after a 12-h overnight fast for blood collection and biochemical analysis (blood count, fasting blood glucose, HbA1c levels, triglycerides, total cholesterol, low-density lipoprotein *cholesterol* [LDL-c], and high-density lipoprotein *cholesterol* [HDL-c], creatinine and ultra-sensitive *polymerase chain reaction* [PCR] assay). LDL-c levels and glomerular filtration rate (GFR) are calculated as detailed below.
LDL-C = (total cholesterol − HDL-C) − (triglycerides/5);GFR (mL/min/1.73 m^2^) = 175 × creatinine^−1.154^ × age^−0.203^ × 1.212 (for blacks) × 0.742 (for females) [31].

Volunteers are then offered a standard snack and asked to rest in a dark, quiet room at 23–24 °C for 10 min. Arterial stiffness is assessed by carotid-femoral pulse wave velocity (PWV) [32] using the Complior Analyse (ALAM Medical, Paris, France). The straight distance between the two arterial sites is measured with an infantometer and data on BP, height, total body mass, and distance between carotid and femoral artery sites are entered into the measuring device software for PWV calculation [32].

The volunteers then undergo the one-repetition maximum (1-RM) test to assess lower limb maximum strength [33] in a proper exercise room at the study site. They first learn the exercise techniques and are instructed on how to perform knee extension, knee flexion, leg pressure, and plantar flexion exercises on a guided weight machine (Movement Perform W8; São Paulo, Brazil). Warm-up consists of 10–12 repetitions, 30% of 1-RM (2 concentric: 2 eccentric phases controlled by a metronome). After a rest of 3–5 min, they start the 1-RM test. It is interrupted to adjust the load when they are able to perform more than one repetition or when they are not able to lift the load. A 5-min rest is allowed before a new attempt is made. The 1-RM is determined when the volunteer performs one complete movement [33]. Their BP is measured 5, 10, and 15 min after the end of the test. The study interventions are scheduled afterwards.

### Visits 3 and 4: α1-adrenergic receptor blockage, assessment of endothelial function, autonomic nervous system activation, and exercise intervention

#### α1-adrenergic receptor blockage

α1-adrenergic blockage is used to assess the effects of sympathetic nervous system (SNS) activation on FMD in response to exercise as described in the literature [26]. Since prazosin is no longer available in Brazil, its analog doxazosin is used in this study [34]. Briefly, 90 min before the start of the exercise intervention, the volunteers are asked to take a tablet containing either placebo (microcrystalline cellulose) or an *α*1-adrenergic blocker (doxazosin 0.05 mg kg^−1^ of body weight) and to lie down and rest. This dose of an *α*1-adrenergic blocker has been reported as being able to block 80% of α1-adrenergic receptors in studies of sympathetic activation and vascular responses [35–37].

An independent researcher blinded to the study intervention gives a tablet to the volunteer on the day of the exercise session according to previous random assignment.

#### Assessment of endothelial function

endothelial function is assessed by FMD as described elsewhere [38, 39]. In a quiet, dark room with controlled temperature (23–24 °C) at the study site, a qualified evaluator blinded to the intervention condition simultaneously measures blood flow velocity and baseline brachial artery diameter on the volunteer’s right arm. With the volunteer in supine position, arm extended and across the trunk at an angle of ~ 40° after a 10–15-min rest, measurements of baseline BP (left arm), resting HR, blood flow velocity, and brachial artery diameter are taken. They are to be evaluated 10 min before and 10, 40, and 70 min after the exercise session.

For the assessment of FMD of the brachial artery, the volunteers are asked to come to the study site after 6-h fasting except for anti-hypertensive medication. A rapid deflation cuff (Incoterm™ EC500; Porto Alegre, Brazil) is placed around the forearm 5 cm distal to the antecubital fossa, and B-mode artery images are obtained at the distal third of the arm with a linear multi-frequency transducer (12 MHz) connected to a high-resolution Doppler ultrasound system (Esaote MyLab™ 70 XVision; Genoa, Italy). The positions of the ultrasound probe and the cuff are marked on the skin so that they can be reproduced during the study. The position of the arm is photographed and the distance between the transducer and the antecubital fossa is measured so that the same can be reproduced in the second exercise session. The evaluator aligns the cursor of the sample volume to the width of the artery at an insonation angle of 60°. Baseline diameters are recorded for 1 min and the forearm cuff is inflated to 50 mmHg above systolic blood pressure (SBP) for 5 min. Images are recorded 30 s before cuff deflation and for 3 min after cuff deflation. Real-time Doppler ultrasound images are recorded and stored into a USB video card (Dazzle; Taiwan) for offline data analysis. To minimize bias blood flow velocity and brachial artery diameter are evaluated via an edge-detection and wall-tracking software program (CardiovasculareSuit™; Pisa, Italy). From this synchronized brachial artery diameter and blood flow velocity data, blood flow (the product of lumen cross-sectional area and Doppler velocity) is calculated at 30 Hz. Forearm peripheral vascular resistance is determined as mean BP divided by blood flow. FMD is calculated as the percentage change in peak diameter after cuff deflation from baseline. Time to peak diameter is calculated from the point of cuff deflation to peak artery diameter [39]. The shear rate is calculated (4 × mean blood velocity/artery diameter) as the area under the curve between the *point* of deflation *and* maximal *dilation* [12].

#### Evaluation of autonomic nervous system activation

ANS activation is evaluated through heart rate variability (HRV) and blood pressure variability (BPV) as described by Atala et al. [40]. Data are collected through continuous non-invasive measurements of pressure waves using digital photoplethysmography (Finometer®, Finapres Medical System BV, Netherland). A cuff device is worn on the middle finger of the right hand coupled to an analog-to-digital converter (AT/MCA-CODAS, DATAC Instruments Inc., Akron, Ohio, USA). Continuous signal sampling acquisition is obtained at 1000 Hz after resting (lying down for 10 min) before FMD. The readings are made for 10 min before forearm cuff inflation for all volunteers either on the placebo or α1-adrenergic blocker groups.

Data are recorded into BeatsScope® (Smart Medical, Gloucestershire, United Kingdom) and LabChart® (ADInstruments, Sydney, Australia) software programs for data analysis of histograms showing BPV and pulse interval series (RR interval) for power spectrum analysis (HRV). All heartbeats are identified through a specialized algorithm using MAT-LAB MT (MATLAB 6.0, Mathworks, USA) with automatic detection of systolic and diastolic pressure wave events. Pulse intervals (PIs) are calculated as the difference between start and end points of the cycle (PI = time point 1 − time point 0). For the time-domain analysis of HRV and BPV data, such as spectrum composition (fast Fourier transform), the CardioSeries® software program is used (www.danielpenteado.com/cardioseries). This analysis requires the removal of transient and discrepant elements and interpolation of consecutive fragments of a time series. The following spectral frequencies are evaluated: very low frequency (VLF, 0.007–0.04 Hz); low frequency (LF, 0.04–0.15 Hz); high frequency (HF, 0.15–0.4 Hz); and total power (TP, VLF + LF + HF). Spontaneous baroreflex sensitivity (SBE) is inferred by the square root of (LF/HRV m^2^)/(LF/BPV m^2^) [40].

#### Aerobic exercise protocol

AE session is performed on a horizontal cycle ergometer (Movement BM4500 Pro, São Paulo, Brazil) and consists of warm-up (5 min) followed by moderate-intensity AE (60% HR reserve) for 40 min. The volunteers are monitored using a heart rate monitor (POLAR^TM^ RS800CX RUN, Helsinki, Finland) and a subjective effort scale (Borg scores 6 to 20). BP and HR measures and Borg scores are recorded at the start, every 5 min during the session, and up to 15 min after exercise.

#### Resistance exercise protocol

RE consists of lower limb exercise (knee extension, knee flexion, leg pressure, and plantar flexion exercises) on a guided weight machine (Movement Perform W8; São Paulo, Brazil), 4 sets with 12 repetitions, 60% of 1-RM (2 concentric: 2 eccentric phases controlled by a metronome). There is a 90-s rest between sets and exercises and the session lasts 40 min. BP, HR, and Borg scale are recorded at the start and end of set 4 of each exercise as well as up to 15 min after exercise. While performing lower limb strength exercises, the volunteers are not be allowed to hold the hand rests, and an adjustable seat belt is used to stabilize the hip during knee extension and knee flexion [33].

#### Combined exercise protocol

CE consists of AE for 20 min + RE for 20 min (two sets of each exercise) as described elsewhere. Similarly, BP, HR, and Borg scores are recorded at the start and end of RE as well as at the start, every 5 min, and up to 15 min after AE.

#### Additional information

The stress exercise test, 1-RM test ,or exercise session are not started when resting BP is greater than 160 mmHg (SBP) and/or 105 mmHg (DBP) [42]. If BP remains above the recommended levels at a second check the volunteers are referred to the study cardiologist for evaluation. They will be excluded from the study if the cardiologist determines that they cannot participate.

The potential risks and discomforts that volunteers may experience during the experiment include: (i) discomfort due to pressure on their arm when the cuffs are inflated for ultrasound examination (FDM assessments); (ii) discomfort due to pressure on their finger for continuous blood pressure and heart rate monitoring (evaluation of ANS); (iii) “delayed-onset muscle soreness” may occur after exercise; (iv) the blood pressure medication (doxazosin) and its related dose have been used in other studies; however, doxazosin may cause few symptoms including nausea, dizziness, and low blood pressure, which may or may not lead to syncope (fainting).

#### Data management

to ensure data security and data integrity, all research data will be initially collected on printed forms and recorded by each researcher ([name] and [name]) according to the established procedures. The research project coordinator ([name]) will check the forms for unreadable/illegible entries, inconsistent data and missing information. A collaborator blinded to the study intervention will enter and store data from all forms into the REDCap platform at the study site under the supervision of one of the contributors ([name] or [name]). Only the authors of this study will have access to it. Each participant has the right of access to their own research results.

After completion of data collection and analysis, relevant data and research findings will be disseminated by preparing research papers for publication in scientific journals with no involvement of professional writers. The dataset will be made available upon publication according to individual journal guidelines.

### Statistical analysis

A per-protocol (PP) analysis will be conducted. The Shapiro-Wilk is used to test the normality of data. Values are presented as means ± standard deviations or medians and 95% confidence intervals (95% CIs) according to the distribution of variables. A multivariate analysis of data is performed using the generalized estimation equations (GEE) for repeated measures with Bonferroni’s post hoc. Pearson’s and Spearman’s tests are used to assess potential correlations between variables according to their distribution. Statistical analyses are carried out using the Statistical Package for Social Sciences (SPSS) 24.0. A level of significance of < 0.05 is set for all analyses.

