### Eligibility criteria

Recruitment will be through on-site screening, media postings, and patient databases. Thus, hypertensive male and female individuals aged 35 to 55 years receiving health care at the study site, using anti-hypertensive drugs, who do not engage in regular physical exercise (≥ 2 sessions per week) are eligible to participate. Exclusion criteria are individuals with diabetes mellitus; chronic renal failure; body mass index (BMI) ≥ 35 kg/m^2^; coronary artery disease; heart failure; users of beta-blockers and/or alpha-blockers; smoking; lower limb injuries that prevent them from engaging in the study intervention; and females aged 35 to 55 with menopause. If doxazosin induces a change in exercise workload or a reduction in blood pressure to levels that would affect exercise performance, the volunteer will be excluded from the study. If a volunteer drops out before completing both study interventions (α1-adrenergic blocker or placebo), we will make an effort to reach them and find out the reasons behind it. If their decision is final, it will be considered “subject withdrawal” and their data will be excluded from the final analyses.

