### Sample size

The sample size is calculated according to Atkinson et al. [26]. In their study, they compared endothelium-dependent vasodilation (by FMD) after a single session of moderate-intensity AE for 30 min in healthy individuals receiving an α1-adrenergic blocker (prazosin 0.05 mg/kg^−1^) or placebo and reported a *difference in means of* 3.1% with standard deviations (SDs) of 1.13% for placebo and 1.91% for prazosin. For finding a similar difference in FMD (3.1%) between these two conditions (α1-adrenergic receptor block versus placebo) after our protocol’s exercise session (AE, RE, and CE) considering *α* = 0.05 and 80% power, a sample of five volunteers per group (*n* = 15) is required.

For a comparison of FMD measurements among exercise types (AE, RE, and CE), our sample calculation is based on pre-exercise SD (1.18%) and post-exercise SD (1.91%) for the prazosin group as described by Atkinson et al. Thus, to find a difference in FMD of 1.62% considering *α* = 0.05 and 80% power, a sample of 10 individuals per group (*n* = 30) is required. Assuming a 30% loss, a sample of 39 individuals would be required (*n* = 13 per group).

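### GEE on about 10 volunteers per exercise group: unless a small-sample correction is used, the usual robust Wald tests exceed the stated 5% error rate, from about 7% to about 23% depending on the test

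*Protocol article*

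**What the plan says.** The protocol article, under Statistical analysis, states: "A multivariate analysis of data is performed using the generalized estimation equations (GEE) for repeated measures", with Bonferroni post hoc comparisons. It adds that "Statistical analyses are carried out using the Statistical Package for Social Sciences (SPSS) 24.0" and that "A level of significance of < 0.05 is set for all analyses". It does not name a variance estimator, working correlation, test statistic or set of model terms.

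The number of clusters follows from other sections. Sample size asks for "80% power, a sample of 10 individuals per group", 30 in all, raised to 39 (13 per group) for losses. The analysis keeps completers only: "A per-protocol (PP) analysis will be conducted", and for withdrawals, "their data will be excluded from the final analyses".

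The layout follows from Randomization and blinding, which gives three exercise types between volunteers and two conditions crossed within volunteer, and from Assessment of endothelial function, where FMD is measured "10 min before and 10, 40, and 70 min after the exercise session".

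**The concern.** The sandwich variance used with GEE and its chi-square Wald test are justified when the number of clusters is large. Here the cluster is the volunteer. With few clusters the sandwich variance is biased downward, and the normal or chi-square reference ignores the uncertainty in the variance. Both faults make p-values too small and confidence intervals too narrow.

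The tests most exposed are close to the research question. The tablet is taken 90 min before exercise and the first FMD is taken 10 min before exercise, so the pre-exercise value is already under drug. A pooled condition main effect therefore mixes a resting drug effect with the drug's effect on the response to exercise. The second of these is carried by condition-by-time and by contrasts within an exercise type, and these rest on the fewest clusters or the most degrees of freedom.

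**Working it through.** **Inputs from the article.** Evaluable volunteers: 10 per group. Recruited: 30 × 1.3 = 39, or 13 per group. Completers if 30% of 39 are lost: 39 × 0.7 = 27.3, about 9 per group. Cells: 3 × 2 × 4 = 24. Nominal level 0.05, taken as two-sided.

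**Assumptions, not in the article.** Saturated cell-means model; complete, normally distributed data; equal covariance across exercise groups; uncorrected robust sandwich with chi-square Wald tests.

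**Bias in the standard error.** With balanced complete data the robust variance of a cell mean is Σr²/n², whatever the working correlation; actual GEE fits under independence and exchangeable structures agreed with this. The unbiased version is Σr²/[n(n−1)]. At n = 10 the ratio is 9/10, so the standard error is multiplied by √0.9 = 0.949.

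**One-df contrasts (exact).** True size = 2·P(t_ν > z·√((n−1)/n)), where ν = n−1 within one exercise type and ν = 3(n−1) when pooled.
- Within one type, n = 10: 1.96 × 0.949 = 1.859; 2·P(t₉ > 1.859) = 9.6%.
- Pooled condition effect: 2·P(t₂₇ > 1.859) = 7.4%.
- Interval width within one type: the multiplier used is 1.859 where t₉ needs 2.262, a ratio of 0.82.

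**Three-df condition-by-time (exact).** The Wald statistic is Hotelling's T² times n/(n−1), and T²(ν−q+1)/(νq) follows F(q, ν−q+1). With q = 3 the chi-square cut-off is 7.815, and 7.815 × 0.9 = 7.033.
- Pooled (ν = 27): 7.033 × 25/81 = 2.171; P(F₃,₂₅ > 2.171) = 11.7%.
- Within one type (ν = 9): 7.033 × 7/27 = 1.823; P(F₃,₇ > 1.823) = 23.1%.

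None of these exact figures depends on the correlations. The 2-df and 6-df between-group tests were simulated with normal data, and hardly moved with the assumed correlations.

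| Test | 9 per group | 10 per group | 13 per group |
|---|---|---|---|
| Pooled condition main effect (1 df) | 7.7% | 7.4% | 6.8% |
| Drug–placebo contrast within one type (1 df) | 10.2% | 9.6% | 8.4% |
| Exercise; exercise × condition (2 df, simulated) | 11% | 10% | 9% |
| Time; condition × time, pooled (3 df) | 12.6% | 11.7% | 9.8% |
| Condition × time within one type (3 df) | 25.9% | 23.1% | 17.7% |
| Exercise × time; three-way (6 df, simulated) | 26% | 23% | 17–18% |

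**Bonferroni.** Take nine contrasts as an illustration (three post-exercise times in three exercise types). The level is 0.05/9 = 0.56%, with z = 2.773. At n = 10, 2.773 × 0.949 = 2.631 and 2·P(t₉ > 2.631) = 2.7%, about five times nominal. The adjustment moves the threshold further into the tail, where the normal reference is worse.

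**Model-based errors instead (exchangeable, 10 per group, simulated).** If all correlations are equal (0.5), sizes run from about 4% to 8%. If same-visit correlation is 0.5 and across-visit 0.3, the condition main effect rejects about 17% and exercise × condition about 22%, while condition × time rejects about 2%.

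**Corrected methods.** Mancl–DeRouen variance with an F reference (27 denominator df), 10 per group: about 4–5% for the pooled 1- to 3-df tests and about 9% for the 6-df tests. Split-plot/mixed-model F-tests, simulated with same-visit correlation 0.65 and across-visit 0.5, rejected between 4.7% and 6.3%.

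**The case against.** The strongest reply is that the article never says its tests are robust, Wald or uncorrected. It is a condensed account, and such details may properly sit in a full protocol or SAP that is not shown. That stands: silence on the estimator is not itself a fault, and the figures are conditional. With model-based errors and a truly exchangeable correlation, the excess is small or absent. What the article does fix is GEE, the 0.05 threshold and the number of volunteers. In that setting neither common uncorrected form secures 5% across the planned tests. The two sessions are 5 to 7 days apart, so a higher correlation within a visit than across visits is plausible.

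A reader might infer that the plan commits to a method that rejects true nulls two to five times too often throughout. The document does not support that. The estimator is unstated; the pooled drug–placebo effect is inflated only about 1.5-fold (7.4/5); and with 13 completers per group the worst case is about 3.6-fold. The four- to five-fold figures belong to the 6-df interactions, to condition-by-time within one type, and to a contrast at 0.05/9. The article names none of these tests explicitly.

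The mixed-model benchmark is favourable to the remedy: the data were simulated with the covariance that the model assumes. Serial correlation across the post-exercise times and unequal variances were not tested, although Sample size quotes unequal SDs (1.18% and 1.91%).

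Finally, the article calls the trial exploratory. That lowers the stakes, but a powered sample size and a 0.05 threshold for all analyses still claim an error rate that should be real.

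**Conclusion.** The concern holds in conditional form. GEE is a large-sample method chosen for about 9 to 13 analysed volunteers per exercise group and 24 cells. Under uncorrected robust Wald tests in a saturated model at 10 per group, the 5% level becomes about 7% for the test least affected and about 23% for the tests most affected. The premise is an inference about usual practice, not something the article states. The arithmetic also assumes normal, complete data with equal covariance across groups. Given the exploratory label, this should be settled before analysis; it does not invalidate the design.

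**What to change.** In Statistical analysis, make the primary analysis a linear mixed model fitted by REML. Use random volunteer and volunteer-by-session effects (or another suitable within-volunteer covariance), and fixed exercise, condition, time and their interactions. Use Satterthwaite denominator degrees of freedom, or Kenward–Roger where the software offers it. Apply Bonferroni to the resulting p-values.

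If GEE is kept, name the estimator and use a bias-corrected sandwich with a t/F reference. State that the 6-df interaction tests would still reject about 9% under the null.

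The cost is a few sentences; no new data are needed. The article does not show which corrections SPSS 24.0 provides, so that must be checked. Intervals widen and p-values rise. For a drug–placebo contrast within one type at 10 per group, the interval grows by about 10% if variance is pooled over 27 df (2.052/1.859 = 1.10), or about 22% on 9 df (2.262/1.859 = 1.22).
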